## APPENDIX 9: PHARMACOGENETICS AND POPULATION PHARMACOKINETICS

### TITLE

Relationship between plasma drug concentrations (pharmacokinetics, PK), virological response (pharmacodynamics, PD), and drug disposition genes (pharmacogenetics, PGx) - Protocol summary

### DOCUMENT VERSION AND DATE

V1.0, October 21, 2009

### RATIONALE

Many factors influence the effects of medications, including age, organ function, concomitant therapy, drug interactions, and the nature of the disease. Moreover, there are now numerous examples of cases in which inter individual differences in drug response are due to sequence variants in genes encoding drug-metabolising enzymes, drug transporters, or drug targets. It is well recognised that different patients respond in different ways to the same medication.

Despite huge advances in terms of the impact of antiretroviral therapy on HIV-related morbidity and mortality patients continue to fail therapy.

Most first-line regimens for the treatment of HIV are now similar in potency and, assuming susceptibility to the selected regimen determined by genotypic resistance testing, tolerability and toxicity are the key issues differentiating currently available agents.

Importantly, drug concentrations and drug disposition gene patterns may explain virological failure or development of toxicity in HIV-infected patients. Previous studies have shown that approximately 30% of patients have low drug concentrations and these have shown to be associated to virological failure [Alexander et al. Antiretroviral concentrations in untimed plasma samples predict therapy outcome in a population with advanced disease. J Infect Dis 2003;188:541-8].

This ancillary study allows for identifying what subgroup of patients fails therapy, or develops toxicity, for pharmacological reasons.

The relation between drug concentrations and adherence is investigated in order to assess the percentage of patients failing therapy, or developing toxicity, because of drug plasma exposure.

### OBJECTIVES

- To investigate the relationship between drug plasma exposure (PK) and drug disposition genes (PGx)
- To investigate the relationship between drug plasma exposure (PK) and virological response (PD, achieving and maintaining of undetectable viral load)

### ENDPOINTS

- PK/PGx relationship for raltegravir, darunavir/r, and tenofovir
- PK/PD (in terms of efficacy and toxicity) relationship for raltegravir, darunavir/r, and tenofovir

## SUB-STUDY COMPONENTS AND PROCEDURES

- PGx written consent form: PGx written consent form is to be signed at baseline (W00) or at any later visit during the study if more convenient for the Investigator or the study participant.
- The following blood samples are scheduled for the (1) PGx and (2) PK/PD substudy:
  1. One EDTA (1.5 ml) bottle for storage at any time during the trial (after signature of pharmacogenomics consent). This sample is to be frozen in one aliquot of 1.5 ml full blood and shipped at -80°C to a centralised laboratory for the determination of drug disposition genes (PGx).
  2. 10 ml in EDTA bottles and preparation of 4 aliquots of 1 ml plasma for storage at W04 and W24. These samples are to be stored at -80°C and may be used for the later determination of drug plasma concentrations.

**Important:**

    - A) 2. must be spun and plasma isolated and frozen at -80°C until shipment (4 aliquots of 1 ml of plasma).
    - B) Blood samples for the determination of plasma concentrations must be taken  $\geq 5$  hours post-dose in order to be able to project trough concentrations
    - C) Time of previous dose and blood sampling must be reported
- All blood samples aimed at PGx investigations must be anonymised.

Analysis is coupled with adherence assessments

### SAMPLE SIZE:

whole 800 patient population (PGx analysis must not be performed when PGx separate written consent is not obtained)

### PARTICIPATING CENTRES: All

## APPENDIX 10: VIRAL SUB-TYPE ANALYSIS

### TITLE

HIV-1 subtype determinants of outcome

### DOCUMENT VERSION AND DATE

V2.0, November 19, 2010

### RATIONALE

HIV-1 group M is divided into multiple genetic forms, termed subtypes, or clades. Through founder effects, these subtypes have become established in geographically defined areas of the world, and within specific risk groups. The established North American and European epidemics have been characterized by subtype B virus. Thus, the vast bulk of data on responses to therapy and emergence of resistance within randomised studies is from subtype B virus. One major advantage of the NEAT European network is to allow questions to be asked on comparative ART data from an array of subtypes. Through inclusion of Eastern European countries, and infected individuals who have migrated to Europe from Africa and Asia, we are uniquely positioned to address viral subtype issues.

There are a number of reasons why NEAT 001/ANRS 143 is appropriate to subtype analysis

- a) the natural variation of HIV-1 integrase between subtypes identifies some minor resistance mutations (identified in subtype B) which are present as normal polymorphisms in other subtypes. It remains unclear whether these differences impact on clinical response to raltegravir.
- b) Some workers have suggested that the K65R mutation in HIV-1 reverse transcriptase more commonly arises in subtype C than other subtypes. It follows that the genetic barrier may be lower for emergence of resistance in this subtype. Since this is best studied in treatment lacking ZDV (which antagonizes the emergence of K65R), it is particularly relevant to the TDF containing arms in NEAT 001/ANRS 143.
- c) The current darunavir resistance algorithm includes a number of mutations (albeit minor mutations) which are present as polymorphisms in non- subtype B viruses. Whether their presence in drug naïve individuals indicates a lower threshold for viral rebound and emergence of additional resistance mutations is unknown.
- d) It is recognized that gag mutations may impact on PI susceptibility, with or without corresponding protease mutations. The interaction of gag and protease is inextricably linked, and subtype-specific polymorphisms in gag may alter the genetic path to PI resistance

These questions are important for establishing an optimal evidence base to guide management of the heterogeneous patient population within Europe.

### OBJECTIVES

- To compare responses to each arm of the study, across subtypes
- To assess whether subtype is an independent variable in determining response to therapy (in view of the overlap between subtype and risk group/ethnicity, input from the data analysis group is required for this)
- To determine whether subtype specific patterns of emerging resistance to each of the two arms can be discerned, by comparison with baseline HIV-1 sequence

- To identify baseline mutational associations with failure of specific regimens (e.g. integrase for RAL, protease for DRV and RT for tenofovir)
- To verify the phenotype of novel mutations/sets of mutations observed within the trial, by mutagenesis of subtype specific HIV-1 vector systems (in contrast to the standard use of subtype B viruses for commercial phenotypic investigations). This includes exploring gag-protease interrelationships for those failing PI therapy.

#### ENDPOINTS

- Determination of time to treatment failure, overall, as well as by arm, by subtype of virus
- Description of mutational changes associated with resistance
- Identification of mutations predictors of resistance. For instance, integrase mutations in case of RAL treated individuals

#### STUDY COMPONENTS AND PROCEDURES

##### Samples

All patients recruited to this sub study.

1. Screening: Genotype is assessed in the local laboratory (if not previously available).
2. W00 sample – 10 ml plasma for HIV-1 RNA. An aliquot of at least 1 ml is stored frozen and stored (biobank). It may later be sent to a central laboratory responsible for additional genotype testing or if no FASTA file is available in the case of historical genotype testing.
3. At first HIV-1 RNA  $\geq$  500 copies/ml after 32 weeks: HIV-1 genotype is assessed in the local laboratory. In addition, 1 ml of plasma is stored and frozen (biobank). It may later be sent to a central laboratory responsible for additional genotype testing.

##### Sequencing

Reverse transcriptase and protease genes are sequenced in the local laboratories at screening and time of virological rebound. Additional sequencing (e.g. integrase, complete gag gene) may be performed by centralised laboratories using biobank samples. Nucleotide sequences are entered into the central NEAT Virology Group database. Interpretation is undertaken centrally using Virology Sub group algorithm.

##### Phenotype

In selected cases, where a unique set of resistance mutations are observed:

- a) to insert specific mutations emerging in those failing therapy into subtype specific HIV-1 vectors, to assess the drug susceptibility implications
- b) to identify potential gag mutations, within individuals subtypes

##### Analysis

Subtype is determined on all screening sequences by use of the on line Rega algorithm (<http://jose.med.kuleuven.be/subtypetool/html/index.html>)

# APPENDIX 11: RENAL FUNCTION STUDY

## TITLE

Renal function study

## DOCUMENT VERSION AND DATE

V1.0, October 21, 2009

## RATIONALE

Multiple reports have indicated that the antiretroviral drug tenofovir has renal toxicity. Secondary analyses from clinical trials comparing antiretroviral regimens suggest that the risk of tenofovir toxicity is low (1%-2%). In contrast, in the Johns Hopkins cohort, use of tenofovir was associated with a greater decline in renal function than was use of alternative nucleoside analogue. The relative decline in creatinine clearance ( $CL_{Cr}$ ) associated with the use of tenofovir, compared with that associated with the use of alternative nucleosides, was 4%.

In addition, tenofovir administration has been associated with Fanconi's syndrome, which is characterised by hypophosphatemia, hyperphosphaturia, glycosuria, and aminoaciduria; skeletal complications of this syndrome include osteomalacia.

The long-term impact of tenofovir on renal function is still unknown.

Two regimens are to be compared in NEAT 001/ANRS 143:

- darunavir/ritonavir + tenofovir/ emtricitabine
- darunavir/ritonavir + raltegravir

NEAT 001/ANRS 143 thus offers a good opportunity to compare the nephrotoxicity risk of a tenofovir containing regimen with a tenofovir-sparing regimen.

Calculated creatinine clearance is a useful, and probably the only feasible, measurement to assess glomerular function.

Relevant proximal tubular dysfunction is possible without a relevant reduction in glomerular filtration.

There are no established diagnostic criteria for renal tubular function, and even the Fanconi Syndrome lacks a quantitative definition. Moreover, tubular dysfunction is a continuum of mild to severe losses of function.

Measuring tubular function with isolated serum and urine markers is insufficient, because these markers have a very low specificity. By contrast, fractional excretion equations for phosphate and uric acid, as well as normoglycemic glucosuria, are considered specific for proximal tubular function and can be easily and cheaply measured. As a clearcut definition of proximal tubular dysfunction is not available, fasting urine and serum samples are stored at the important timepoints to be able to measure more expensive markers in selected patients.

## OBJECTIVES

- To compare changes in renal function between the two treatments strategies
- To compare proximal renal tubular function between the two treatment strategies

## ENDPOINTS

- Proportion of patients with reduced glomerular function at W48 and W96, defined as at least 25% reduction in calculated GFR (sustained in two measurements at least one month apart)
- Proportion of patients with pathological Proximal Renal Tubule Dysfunction (PRTD) at W48 and W96, defined as one of the following:
  - a) fractional excretion of phosphate > 20% (>10% in patients with concurrent hypophosphatemia) or
  - b) a score of at least 3 out of the 4 following:
    - pathological fractional excretion of uric acid
    - euglycemic glucosuria
    - pathological protein/creatinine ratio in urine
    - low serum bicarbonate
- Change from baseline in glomerular filtration rate as measured by Cockcroft-Gault formula at W48 and W96
- Change from baseline in glomerular filtration rate as measured by MDRD formula at W48 and W96
- Cystatin-C serum levels at W48 and W96
- Protein:Creatinine ratios (Urine) at W48 and W96

## STUDY COMPONENTS AND PROCEDURES

### Planned assessments:

- **Serum:** Potassium, phosphate, creatinine, alkaline phosphatase, gamma-glutamyltransferase and alanine aminotransferase, uric acid, bicarbonate, sample for freezing.
- **Urine spot:** Creatinine, protein, phosphate, uric acid, glucose; dip stick test for leukocytes, erythrocytes, proteinuria and glucosuria, pH; sample for freezing.

### Timepoints:

W00, W04, W12, W48, W96 in fasting state

### SAMPLE SIZE:

whole 800 patient population

### PARTICIPATING CENTRES: All

## APPENDIX 12: QUALITY OF LIFE ASSESSMENTS

### TITLE

Health-related quality of life in HIV-infected people

### DOCUMENT VERSION AND DATE

V1.0, October 21, 2009

### RATIONALE

Guidelines recommendations for treatment in HIV infection are generally based on the information obtained in clinical trials. Traditionally, this has been mostly represented by immunological and virological response and by a safety profile defined through the adverse events occurring during the study. Such measures, however, provide only an incomplete assessment of the composite effects of treatment, and lack information that comes directly from the patient. Therefore, patient reported outcomes (PRO) now play an important role both in research and clinical practice in the evaluation of patients' health status. Health-related quality of life (HRQoL), a complex PRO referring to all the aspects of a person's well-being, has recently been recognised by guidelines as a main therapeutic objective and is therefore increasingly used in the comparison of anti-HIV drugs and as an additional or independent measure of drug evaluation.

To date, suppression of HIV is possible in the vast majority of patients with a wide variety of regimens. However, each of these effective HAART regimens may differ in their associated limitations, such as differences in side effect profiles and differences in convenience of regimens. This leads to questions such as how regimens with comparable efficacy but different side effect profiles should be weighed against each other, and how potency should be weighed against tolerability and convenience. Therefore, it is investigated whether specific benefits and limitations associated with each of the treatments arms of the NEAT 001/ANRS 143 trial translate into differences in patients' health-related quality of life.

### OBJECTIVE

- To compare during follow up the effects of the two different regimens on health related quality of life (HRQoL), self-reported symptoms, treatment satisfaction, and depression.

### ENDPOINTS

To compare the two different regimens in terms of:

- change of quality of life from baseline (even considering strata according to different levels of CD4, HIV RNA, symptom score)
- time to change of quality of life score (EQ-5D and list of patients reported outcomes)
- changes in QoL measures are compared with efficacy data (responses in terms of CD4 and HIV-RNA, clinical progression – AIDS and non-AIDS related events and death -), assessing possible correlations.
- changes in QoL measures are compared with safety data (toxicity, grade 3-4 or any grade), assessing possible correlations.
- changes in symptom patient-reported score are compared with safety data (toxicity, grade 3-4 or any grade), assessing possible correlations.

- changes in QoL measures are compared with adherence data
- differences in QoL changes between patient with HIV/HCV coinfection and patient with HIV infection
- differences in QoL changes between patient with lipodystrophy and patient without lipodystrophy

#### SUB-STUDY COMPONENTS AND PROCEDURES

Instruments of the study are:

- a) A generic HRQoL questionnaire: EQ-5D (it is a brief measure of generic HRQL with established reliability and validity. The EQ-5D is available in many languages and can also be used to calculate quality adjusted life years).
- b) HIV specific symptom scale (22 among the most experienced symptoms are listed with 5 possible options ranging from not at all to very much; a total score is calculated);
- c) CES-D for the assessment of depression (a short version of 10 items is used);
- d) HIVTSQs for the treatment satisfaction assessment (The trial treatment arms differ with respect to the number of daily doses, with one treatment arm having once daily dosing and the other treatment arm having twice daily dosing. Therefore, it is relevant to supplement the HRQL assessment with a measure of regimen convenience and treatment satisfaction).

The QoL assessment are done on the whole population (n=800) at W00, W04, W12, W24, W48, and W96.

No blood sampling is planned.

Analysis is centralised.

Data on HRQoL is matched with pharmacoeconomic data as well as with data on adherence.

### DOCUMENT VERSION AND DATE

V2.0, November 19, 2010

### RATIONALE

The inclusion of sub-studies concerning the issues of pharmacology and medication adherence into the NEAT 001/ANRS 143 trial is highly advisable, mainly because of the potential impact of both these variables on the primary study end-point of treatment efficacy. Many studies have investigated the role of adherence to antiretrovirals as well as of plasma drug concentrations on virological response, however no data is available for more recent antiretroviral drugs and new classes, such as those investigated in the NEAT 001/ANRS 143 trial. Further, because regimen complexity may represent a crucial barrier to optimal adherence, the possibility to control for medication adherence in the statistical analyses might be important, especially in the case of treatment arms dissimilar in terms of daily doses or pill burden.

Another focus of interest is that, at virological failure, adherence-resistance relationships vary according to the different antiretroviral classes and to drug-boosting. This is the result of the complex interplay between the capacity of resistant virus to replicate at different levels of drug exposure and its genetic barrier. In this context, the study of adherence and pharmacokinetic/pharmacodynamic characteristics of new drugs, such as RAL and DRV, would be valuable to describe treatment-specific adherence-resistance relationships.

Finally, the assessment of adherence to innovative treatment regimen could be essential to better understand its association with both toxicity profiles or quality of life-related issues investigated in other NEAT 001/ANRS 143 sub-studies.

### OBJECTIVES

#### Primary objective

- To compare the extent of adherence across the two different first-line treatment strategies in HIV-1 infected antiretroviral naïve adults over 96 weeks: darunavir/r + tenofovir/emtricitabine vs. darunavir/r + raltegravir.

#### Secondary objectives

To compare the two different regimens in terms of:

- level of adherence required for successful virologic suppression
- relative prognostic value of adherence and plasma drug concentrations on the virological success
- relative prognostic value of adherence and plasma drug concentrations on the risk of resistance mutations to one or more drugs in case of virological failure
- relationship between adherence and drug-specific toxicities
- relationship between adherence and patient-reported quality of life.

## ADHERENCE ASSESSMENTS

- All patients included in the NEAT 001/ANRS 143 trial are systematically evaluated for their adherence behaviour by using:
  - Previously validated patient-administered questionnaire to investigate self-reported adherence in terms of number of omitted doses/pills; number of days of complete adherence to trial regimen; overall estimation of adherence at VAS; timing deviation; drug holidays (modified version of the ACTG questionnaire) at W04, W12, W24, W48, and W96.
  - Pill count

At the start of the study, each subject should receive counselling regarding the importance of dosing adherence to antiretroviral medications. In order to document adherence with the treatment regimen, subjects should be instructed to bring their empty medication bottles to investigators at each study visit and their unused medications bottles at the end of the trial. An exact start and stop date, and the number of tablets dispensed and returned are recorded in the CRF. Pill counts are calculated as the number of pills taken (the number of pills dispensed – the number of pills counted). The number of pills expected to have been taken are calculated by multiplying the daily dose (1/2, 1 or 2 tablets) by the number of days since the date dispensed.

Moreover, at each study visit, patients are asked to complete a self-reported questionnaire (a partially modified ACTG questionnaire) investigating several non-adherence behaviours: overall estimated adherence using Visual Analogue Scale, number of missed doses over the last 4 days, number of days of complete adherence to trial regimen, timing deviation, and unplanned treatment interruption.

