At week 96, treatment discontinuations occurred more frequently with lopinavir/ritonavir than with darunavir/ritonavir (23% vs 17% at week 96, respectively). Overall, there was no statistically significant difference in grade 2-4 potentially drug related clinical adverse events between the darunavir/ritonavir and lopinavir/ritonavir arms (23% and 34%, respectively). The overall incidence of rash-related adverse events (any grade, regardless of causality) was similar in the darunavir/r (15%) and lopinavir/r (13%) treatment groups. Grade 2-4 rash adverse events (all types) possibly related to study treatment were reported in 3% and 1% of the subjects in the darunavir/r and the lopinavir/r treatment groups, respectively. There was one case of Stevens-Johnson syndrome in the darunavir/r arm; although other factors may have contributed to this event, a relationship with darunavir/r could not be excluded. Darunavir was associated with statistically smaller increases in triglycerides, total cholesterol, and HDL cholesterol than lopinavir/ritonavir. The limited influence of darunavir/ritonavir on plasma lipid profiles is in part related to the low daily ritonavir dose, i.e. 100 mg [11].

Like with other protease inhibitors, hepatitis has been reported in patients receiving combination therapy with darunavir/ritonavir. In clinical trials, the rate of occurrence was 0.5%, and patients with preexisting liver dysfunction, including chronic active hepatitis B or C, had an increased risk for liver function abnormalities including severe hepatic adverse

events. Post-marketing cases of liver injury, including some fatalities, have been reported. These have generally occurred in patients with advanced HIV-1 disease taking multiple concomitant medications, having comorbidities including hepatitis B or C coinfection, and/or developing immune reconstitution syndrome [12]. Although a causal relationship with darunavir/ritonavir therapy has not been established, it is recommended to monitor liver transaminases during darunavir/ritonavir therapy, as is the case for other antiretroviral drugs and especially for protease inhibitors.

Altogether, these results suggest that once-daily ritonavir-boosted darunavir could offer advantages over lopinavir/ritonavir. Like all other protease inhibitors, darunavir has a high genetic barrier to resistance. Its favourable tolerability profile, including limited dyslipidemia, makes it an interesting alternative for first-line therapy.

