Patients should start their trial treatment at latest on the day after the baseline visit.

The patient should be informed that he/ she should take all dispensed medication and that only empty containers (drug bottles) and expired study drug should be brought back during the trial. Unused study drug should only be returned to the study centre at the end of the trial in order to allow for drug accountability

Patients participating in the sub-studies may have additional blood and urine sampling or other assessments at this visit (see appendices 15-17).

Patients participating in the Viral and Immunologic Dynamics and Inflammation sub-study have additional blood sampling at Day 2-3 and at W01 (see appendix 15).

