## **7.9 Assessment of treatments**

### **7.9.1 Antiretroviral treatment**

At all study visits, the following details are recorded for any antiretroviral drugs, including the study drugs:

- commercial name of the product
- formulation
- dosage per unit
- prescribed dosage
- start date of this prescribed dosage
- stop date of this prescribed dosage
- reason for discontinuation

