### 7.12.4 Management in the case of treatment limiting adverse events

The investigator should consider temporarily withholding therapy if the severity of the adverse experience is Grade 3 or above and/or if clinically indicated. Such decision to interrupt therapy should take into account the patient's baseline laboratory values and any concomitant medication or clinical condition that could be contributory. At the discretion of the investigator, therapy may generally be reinitiated when laboratory abnormalities or clinical adverse events return to near normal or to baseline values. If the adverse event is considered serious or if exposure to the study drug(s) poses additional potential significant risk to the patient, rechallenge is not recommended.

Whenever study drugs are permanently interrupted, i.e. for > 1 month, the regional CTU should be immediately notified.

A dosing interval adjustment of tenofovir/emtricitabine is recommended in all patients with creatinine clearance 30-49 ml/min (see SmPC). Tenofovir/emtricitabine should be permanently discontinued if creatinine clearance is < 30 ml/min.

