## DERIVED ADHERENCE MEASURES

- From patient-reported assessment:
  - Percentage of doses taken/prescribed
  - Percentage of days of complete adherence to trial regimen
  - Percentage at VAS
- From pill count:
  - Percentage of pills returned/delivered

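### Appendix 13 gives two inconsistent pill-count rules; both score investigator-ordered stops as missed doses, and one also scores surplus supply as missed

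*Protocol*

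**What the plan says.** Under Adherence assessments, Appendix 13 takes pills taken as the number dispensed minus the number counted, and obtains pills expected by "multiplying the daily dose (1/2, 1 or 2 tablets) by the number of days since the date dispensed". It does not write out the ratio, but taken over expected is the evident intention. The same paragraph notes: "An exact start and stop date, and the number of tablets dispensed and returned are recorded in the CRF". The formula does not use those dates.

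Under Derived adherence measures, the only pill-count entry is "Percentage of pills returned/delivered". By contrast, the first self-report entry is "Percentage of doses taken/prescribed".

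The protocol foresees stops that are not the patient's choice. Section 7.12.4 states: "The investigator should consider temporarily withholding therapy if the severity of the adverse experience is Grade 3 or above". It also calls for permanent discontinuation after certain rashes, and section 7.13 for stopping some study drugs in pregnancy. Under section 7.12, patients who stop remain in follow-up to the end of the trial.

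The timing of the count is not uniform. Section 7.4 says: "Unused study drug should only be returned to the study centre at the end of the trial". Section 7.10 places the count at the end of trial treatment. Most visit lists in section 7.5 also include a count of returned drugs.

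**The concern.** Adherence should measure how much of what was prescribed the patient took. Neither pill-count rule does this once the investigator has ordered a stop. The expected-pill rule keeps adding pills for days on which none was prescribed. The supply measure counts whatever was left in the bottles, including tablets the patient was told not to take and tablets that were never needed. The two rules also disagree for the same patient, so an analyst following Appendix 13 could report either.

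Comparing adherence between arms is the primary objective of the adherence study, and relating adherence to drug-specific toxicities is a secondary one. If toxicity stops are more frequent in one arm, that arm's pill-count adherence falls even if every prescribed dose was taken. The relation with toxicity becomes partly circular, because the stop that toxicity causes lowers the adherence score directly.

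**Working it through.** The protocol states no numerical value for this measure, so there is no figure to reproduce. The check applies each stated rule to a patient who takes every prescribed dose.

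Inputs:
- Interval: W80 (day 560) to W96 (day 672), so 672 − 560 = 112 days (Table 1).
- Daily dose: 2 tablets. The percentages are the same for 1 tablet.
- Supply: four 30-day bottles, 4 × 30 × 2 = 240 tablets. Bottle size and number are assumptions; the protocol gives neither.
- Ordered hold: 0, 14, 28 or 56 days (assumed range).

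Formulas:
- A, supply measure in the direction of adherence: 1 − returned/delivered.
- B, expected-pill rule: taken / (2 × 112) = taken / 224.
- C, prescribed-days rule: taken / (2 × (112 − days held)).

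| Ordered hold (days) | Taken | Returned | A | B | C |
|---|---|---|---|---|---|
| 0 | 224 | 16 | 93.3% | 100% | 100% |
| 14 | 196 | 44 | 81.7% | 87.5% | 100% |
| 28 | 168 | 72 | 70.0% | 75.0% | 100% |
| 56 | 112 | 128 | 46.7% | 50.0% | 100% |

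With five bottles (300 tablets), A falls to 74.7% with no hold and 56.0% with a 28-day hold; B and C do not change. So surplus is penalised only under A, and ordered holds are penalised under both A and B.

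A can also misrank patients. A fully adherent patient given 120 days of a one-tablet drug for 112 days returns 8/120 = 6.7%. A patient supplied exactly who takes 95% returns 5%, and so looks the more adherent of the two.

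For a permanent ordered stop, B depends on two things that the text leaves open: which dispensing date starts the clock, and when the drug is counted.
- If counted at the stop date, expected days end there and the bias is near zero.
- If days run from the most recent dispensing, the error is confined to the interval containing the stop.
- If days run from first dispensing to W96, a fully adherent patient stopped at W24, W48 or W72 scores 24/96 = 25%, 48/96 = 50% or 72/96 = 75%.

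Upper bound for an arm mean in that last case: section 2.2.1 reports treatment discontinuations of "23% vs 17% at week 96, respectively" in an earlier trial, the second figure being for darunavir/r. Suppose 17% stop, evenly over 96 weeks, so at W48 on average, all by order and all returning drug at the end. The mean is then lowered by 0.17 × (1 − 48/96) = 0.085, or 8.5 points.

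**The case against.** Several points on the other side stand.

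- **Return timing.** Section 7.10 can be read as a count when that patient's trial treatment ends. On that reading the bias from permanent stops largely disappears. It does not help with temporary holds, after which treatment resumes and the held days remain in the denominator.
- **Recorded dates.** The start and stop dates are mentioned immediately before the formula, so their use may have been intended. The formula as written still runs on all days since dispensing.
- **Dose changes.** The half-tablet daily dose in the formula appears to allow for a changed dosing interval, so such a change need not be scored as missed. A full stop is not covered.
- **Direction.** That a returned percentage rises as adherence falls is a matter of labelling.
- **Deferral to the analysis plan.** Section 9.4 leaves detail to a separate plan. Here, however, the protocol does state rules; they conflict with each other and with the taken/prescribed concept used for self-report.
- **Limited reach.** Three of the four derived measures are self-reported, and pill count is not among the trial's endpoints.

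A reader might infer a larger distortion by running the expected-pill rule over the average follow-up of 121 weeks: 0.17 × (1 − 48/121), about 10 points. The documents do not support this, because the adherence objective is set over 96 weeks. Nor do they show that the 17% were ordered stops; section 2.2.1 gives no split by reason.

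**Conclusion.** The point holds in a limited form. Appendix 13 states two pill-count rules that give different values for the same patient, and neither restricts the denominator to the days on which the drug was prescribed.

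The size for temporary holds follows directly from the stated formulas: a 28-day ordered hold in a 112-day interval costs a fully adherent patient 25 points under the expected-pill rule. Under the supply measure the loss is 30 points with four 30-day bottles, of which 6.7 come from surplus alone. Bottle size, number of bottles and length of hold are assumptions.

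For permanent stops, the bias in an arm mean under the expected-pill rule lies between near zero and about 8.5 points over 96 weeks. The upper end needs every assumption listed with the calculation.

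Two stronger inferences are not supported. Surplus supply is not penalised under both rules, since the expected-pill rule still gives 100%. And no particular spurious difference between arms can be claimed, because the protocol gives no between-arm difference in ordered stops. The effect is confined to the pill-count measure and to the between-arm and toxicity comparisons that use it.

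**What to change.** Use one definition in both parts of Appendix 13:

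adherence (%) = 100 × (pills dispensed − pills returned) / (prescribed daily dose × days prescribed).

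Days prescribed should run from the drug's recorded start date to its stop date, excluding interruptions ordered by the investigator. Interruptions chosen by the patient stay in the denominator. Replace the returned/delivered entry with this measure. State which dispensing date and which count apply, and reconcile sections 7.4 and 7.10 on when unused drug is counted.

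The cost is a wording change in Appendix 13, carried into the analysis plan. Section 7.9.1 already has sites record the start date and the "stop date of this prescribed dosage" for each antiretroviral drug, together with the reason for discontinuation. No new data item is needed, provided temporary holds are entered there as well. No dose or treatment rule changes.
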